## Abstract

**Background:**

Long-Lasting Insecticidal Nets (LLINs) are one of the major malaria vector control tools, with most countries adopting free or subsidised universal coverage campaigns of populations at-risk from malaria. It is essential to understand LLIN durability so that public health policy makers can select the most cost effective nets that last for the longest time, and estimate the optimal timing of repeated distribution campaigns. However, there is limited knowledge from few countries of the durability of LLINs under user conditions.

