### ABCDR components

#### Attrition (A component)

Attrition of LLINs is defined as the proportion of LLINs that are no longer in use as mosquito nets to sleep under in the receiving household after a given amount of time. This is commonly due to loss through nets being damaged, discarded, or used for other purposes than sleeping under. Nets that are sold, given away or stolen will be excluded from the attrition analysis following WHO guidelines [6] as they may still be “serviceable”.

Trained field interviewers will perform the field visits of all households selected from the master list and voluntarily participating in the study during the sampling points (retrospective sampling, 10, 22 and 36 months after prospective LLIN distribution). Questionnaire data will be collected using Open Data Kit (ODK) Collect software (http://opendatakit.org/use/collect/) on Android tablet computers (Google Nexus One). Observations by the field workers on presence and absence of distributed nets, the location of the net (hanging or stored away), fabric integrity and the net condition are included in the questionnaire (Additional file 2).

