### Statistics and data analysis

#### Sample size calculation

Sample size calculations were based on the primary outcome measure of net attrition using the standard formula for the difference between two proportions [47]. The BCD components were treated as an additional sub-sample to the original calculated sample size. Assuming an average of 3 nets per household and a coefficient of variation of 0.25, then the formula on page 110 of Hayes & Moulton [48] gives a sample size of 973 households per arm to detect a difference in attrition between two brands with attrition rates of 47.5% and 52.5% with 90% power. Therefore, there will be at least 90% power to detect a 5% difference in attrition rates. Loss to follow up and households excluded due to sub-sampling have been added to the final sample size to give (1,140 households * 3 nets/ household) = 3,420 LLINs per LLIN product (Table 3).

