#### Data analysis

We will collect a set of response variables (Table 1) and explanatory variables. The explanatory variables will be collected from household questionnaires and observations and will include time after net distribution, net product, geographical location, patterns of net use (e.g. type of bed, frequency of net use), net status, washing and handling, perceptions of nets and socioeconomic status of the household. All response variables will be analysed using the statistical programs STATA^®^13 (http://www.stata.com/) and R (http://www.R-project.org/). Regression modelling including multivariate generalised linear models and generalised linear mixed models will be used to determine covariates affecting net durability components such as LLIN age, geographical location and data collected from household surveys. Principal Component Analysis (PCA) will be used to determine a combination of variables for socioeconomic status to explain the overall observed variation and reduce the complexity of the data. In order to analyse net attrition and physical degradation in more detail, 95% confidence intervals will be calculated for the attrition and ‘unserviceable’ physical condition of each net product at the three prospective time points. At each point, logistic regression with a category for each brand of net will be performed to assess if there is a difference in attrition between the three net products. If a significant difference is found, then pairwise comparisons will be examined.

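### Attrition is tested across brands at 10, 22 and 36 months with no visit named primary; with each test at 5%, the chance of some false brand difference is about 10–14%

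*Protocol article*

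**What the plan says.** All places are in the protocol article.

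- **Primary outcome and size (Sample size calculation).** The section opens by stating: "Sample size calculations were based on the primary outcome measure of net attrition using the standard formula for the difference between two proportions". The inputs are "Assuming an average of 3 nets per household and a coefficient of variation of 0.25", and the formula "gives a sample size of 973 households per arm to detect a difference in attrition between two brands with attrition rates of 47.5% and 52.5" per cent, with 90% power. The section concludes that "there will be at least 90% power to detect a 5% difference in attrition rates". It names no visit.
- **Follow-up (Prospective study).** The same households are surveyed at 10, 22 and 36 months. At each round 48 households per product are sub-sampled and leave later rounds.
- **Brand test (Data analysis).** "At each point, logistic regression with a category for each brand of net will be performed", followed by pairwise comparisons if the result is significant. Attrition by product, with 95% confidence intervals, is also reported at the three visits.
- **Other modelling (Data analysis).** Generalised linear and generalised linear mixed models of the durability components are planned. Time since distribution and net product are among the explanatory variables, and net age is among the covariates to be assessed.
- **Exclusions (Attrition).** "Nets that are sold, given away or stolen will be excluded from the attrition analysis", with WHO guidelines given as the reason.
- **Use of results.** The Abstract's background says policy makers need to "estimate the optimal timing of repeated distribution campaigns", and the Discussion presents campaign timing as a use of the findings.

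**The concern.** The study is sized for one comparison of the primary outcome but tests that outcome three times, and any of the three can lead to a statement that one brand outlasts another. The sizing rates lie near 50%. Attrition accumulates, so it can hardly be near 50% at all three visits, and the article does not say which visit the calculation represents.

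The results are meant to guide national procurement among three named products. A brand difference seen at one visit and not at the others could be reported as the finding, and a reader would have no stated rule for weighing it.

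**Working it through.** **1. The plan's own figure.** The article cites a textbook formula that is not at hand. I assume it is the usual unmatched cluster formula for two proportions:

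c = 1 + (z₁ + z₂)² × [p₀(1−p₀)/m + p₁(1−p₁)/m + k²(p₀² + p₁²)] / (p₀ − p₁)²

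Inputs from Sample size calculation: p₀ = 0.475, p₁ = 0.525, m = 3, k = 0.25, power 90%. Two-sided 5% is my assumption.

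- Bracket: 0.49875/3 + 0.0625 × 0.50125 = 0.16625 + 0.03133 = 0.19758
- c = 1 + (1.960 + 1.282)² × 0.19758/0.0025 = 831.4, so 832 households per arm

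The stated 973 is not reproduced. It is on the safe side: 973 households give 93.9% power with these inputs. An unstated input such as m = 2.5 gives 971. That difference is a separate matter. What counts here is that the calculation covers one two-brand comparison at one unspecified time.

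**2. Error within a visit.** The three-brand test (2 degrees of freedom) comes first and the pairwise tests follow only if it is significant. With three groups, this gate holds the error within a visit at the level of the global test. Only the repetition over visits adds error.

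**3. Error across visits, bounds.** With each global test at 5%, the ceiling is 3 × 0.05 = 15%. Independent tests would give 1 − 0.95³ = 14.3%. The tests are not independent, because losses accumulate in the same nets.

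**4. Error across visits, allowing for correlation.** For cumulative attrition pᵢ < pⱼ in the same nets, the correlation between visits is √[pᵢ(1−pⱼ) / (pⱼ(1−pᵢ))]. At 10% and 30%, for example, it is √(0.07/0.27) = 0.51. Simulating three 2-df tests with these correlations and no brand difference, under attrition patterns that are all assumed:

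| Attrition at 10 / 22 / 36 months | Chance of at least one significant brand test |
|---|---|
| 30 / 40 / 50% | 10.4% |
| 15 / 35 / 50% | 11.9% |
| 20 / 40 / 60% | 12.1% |
| 10 / 30 / 50% | 12.6% |
| 5 / 20 / 50% | 13.2% |
| 2 / 15 / 50% | 13.7% |

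A direct simulation of 3,000 independent nets per brand at 15/32/50% gives 12.1%, with each single test at about 5%. The calculation treats nets as independent, so it takes for granted that household clustering is handled correctly in the standard errors.

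**5. What each remedy costs.**

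- One primary visit at 5%: the error is 5% and the sample size does not change.
- Three co-primary visits at 0.05/3 = 0.0167 each: the error is at most 5%. The formula then asks for about 1,069 households per arm. At 973 households, power falls from 93.9% to 86.7%.

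**6. Households left at month 36.** Two earlier rounds remove 2 × 48 = 96 per product, leaving 1,140 − 96 = 1,044 against the stated 973, so 71 remain for other losses.

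**The case against.** The strongest reply is that a full protocol or analysis plan, not shown, may name the primary visit and a multiplicity rule, as such documents commonly do. The article also states no test level and no rule that a result at any one visit supports an overall brand claim. This has force: the 10–14% is conditional on 5% per test and on reading any significant visit as a positive result. What remains is in the text itself. The article prescribes a brand test at each visit, lets each one open pairwise comparisons, and attaches its only power statement to none of them.

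Three stronger readings are tempting and should not be drawn:

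- **That net lifetime can never be obtained.** Attrition with confidence intervals at three visits gives three points on each brand's retention curve, and the mixed models can include time and product. Campaign timing appears as background need and later use, not as a promised estimate. The article simply names no lifetime summary.
- **That follow-up is wasted, or each visit is treated only as a fresh cross-section.** Sub-sampled households count at every visit up to their removal, and the time-based models stand beside the per-visit tests.
- **That removing 96 of 1,140 households (8.4%) is a defect.** Selection is random, stratified by district and product, and the article says it was budgeted: "Loss to follow up and households excluded due to sub-sampling have been added to the final sample size".

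Excluding sold, given-away or stolen nets is likewise a declared guideline choice, not an error.

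**Conclusion.** The point holds for the three unranked tests of the primary outcome. Under two-sided 5% per global test, correct standard errors and cumulative loss in one cohort, the chance of at least one false brand difference is about 10–14%, at least twice the level of a single test. The 14.3% for independent tests lies just above this range and should not be quoted as the expected value.

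The matter should be settled before the 22- and 36-month data are analysed. It does not invalidate the design. The survival analysis proposed below is an improvement on the plan and does not repair a missing or impossible estimate.

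**What to change.** 1. In Data analysis, name the 36-month three-brand test as the primary comparison, with its significance level, and keep the gated pairwise tests beneath it. Label the 10- and 22-month tests secondary.
2. In Sample size calculation, say that the 47.5% and 52.5% refer to month 36.
3. As a supplement to the per-visit estimates and mixed models, fit one discrete-time (interval-censored) survival model over the three intervals, with brand and household clustering. Censor sub-sampled and lost households at the last survey at which they were seen. Report retention and median net life by brand with confidence intervals.
4. Keep the exclusion of sold, given-away or stolen nets as stated, and add censoring of these nets as a sensitivity analysis.

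Items 1 and 2 cost only wording and no extra households; the price is that the 10- and 22-month tests lose confirmatory status. Items 3 and 4 need modest programming. The Current study status section reports only the 10-month survey as complete, so the choice can still be recorded before the later data arrive.

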#### Retrospective study

Households will be enrolled on written informed consent (Additional file 1). Participants’ houses and questionnaires will be identified by barcodes associated with numeric codes (six-digit serial numbers) to ensure their anonymity and due care will be taken to ensure that only barcodes and numeric codes are used on LLINs and questionnaires, thus blinding participants and researchers to treatment allocation. All the nets from the participating households will be collected and replaced with one of the three new LLIN products (Table 2) chosen at random. The prospective LLIN products will only be known to field teams as net types 1, 2 and 3, thereby blinding and randomising the treatment distribution as much as possible. Each day the field team will receive a household list and a randomly mixed bundle of five sets of type 1, 2 and 3 nets (three nets of same type per set bagged for one household, assuming an average of three sleeping spaces per household). The interviewer will randomly pick one set from the bundle to be distributed when they arrive at each household (modified lottery method). If the household contains more than three sleeping spaces, more nets of the same type will be provided. The interviewer will record the five-digit serial numbers attached to the nets on the questionnaire as described above. Thus, randomisation is conducted by the field workers at the household level, resulting in 15 households per village receiving sufficient nets of one product to cover each sleeping space (Table 3).

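### The brand test and the per-product intervals for attrition are specified without allowance for the household, which is the unit of randomisation and is allowed for in the sample size

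*Protocol article*

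**What the plan says.** In the Retrospective study section, "randomisation is conducted by the field workers at the household level". Nets are handed out as "three nets of same type per set bagged for one household", with more of the same type where a household has more than three sleeping spaces. Allocation is balanced in each village, "resulting in 15 households per village receiving sufficient nets of one product".

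The outcome is counted over nets. The Attrition section has it "defined as the proportion of LLINs that are no longer in use as mosquito nets". It is the primary outcome: "Sample size calculations were based on the primary outcome measure of net attrition".

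The Sample size calculation section allows for correlation within households. "Assuming an average of 3 nets per household and a coefficient of variation of 0.25", a cluster-trial formula is said to give 973 households per arm for 47.5% against 52.5% attrition at 90% power.

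The Data analysis section gives the brand comparison its own sentence. At each of the three follow-up points, "logistic regression with a category for each brand of net will be performed to assess if there is a difference in attrition", with pairwise comparisons if the result is significant. It also says that "95% confidence intervals will be calculated for the attrition and" the unserviceable physical condition of each product. No household term, random effect, GEE or robust variance is attached to either statement. Generalised linear mixed models do appear earlier in the section, alongside ordinary generalised linear models, for identifying covariates of durability. No random effect is specified there.

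**The concern.** Nets in one household share users, washing and the decision to discard, so their outcomes are likely to be correlated. The authors accepted this when they sized the trial. An ordinary logistic regression of net status on brand treats every net as an independent observation and so does not match the design.

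This comparison is meant to inform national procurement, and it is made at three time points with follow-on pairwise tests. If its error rate is above the stated level, a product may be preferred on a chance difference. If the per-product intervals are too narrow, the estimates that feed the timing of repeat campaigns will look more precise than they are.

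**Working it through.** **Inputs from the protocol.** m = 3 nets per household; coefficient of variation k = 0.25; p1 = 0.475, p2 = 0.525; power 90%; 15 households per product per village. Alpha is not stated; two-sided 5% is assumed, in line with the 95% intervals.

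**1. The plan's own figure.** The standard unmatched cluster formula for two proportions is

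c = 1 + (z_α/2 + z_β)² × [p1(1−p1)/m + p2(1−p2)/m + k²(p1² + p2²)] / (p1 − p2)²

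= 1 + 10.507 × [0.16625 + 0.03133] / 0.0025 ≈ 831.4, so 832 households per arm.

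The stated 973 is not reproduced. That is a separate matter: at 973 households the same formula gives 93.9% power, so the claim of at least 90% stands. What matters here is that an ordinary two-proportion calculation needs about 2,100 nets, or 700 households, per arm. The design therefore includes a real allowance for the household.

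**2. Intra-household correlation implied by k.** ICC = k²p/(1−p) at p = 0.5 is 0.0625 × 0.5/0.5 = 0.0625.

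**3. Design effect for nets within households.** DEFF = 1 + (m − 1) × ICC = 1 + 2 × 0.0625 = 1.125. The square root is 1.061, so unadjusted standard errors are about 6% too small.

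**4. True size of a nominal 5% test that treats nets as independent.**
- Pair: 2 × [1 − Φ(1.96/√DEFF)]
- Three brands (2 df): P(χ²₂ > 5.99/DEFF) = exp(−5.99/(2 × DEFF))

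| Household ICC | Source | DEFF | Pair | 2 df |
|---|---|---|---|---|
| 0.02 | assumed | 1.04 | 5.5% | 5.6% |
| 0.0625 | from k = 0.25 | 1.125 | 6.5% | 7.0% |
| 0.2 | assumed | 1.4 | 9.8% | 11.8% |
| 0.4 | assumed | 1.8 | 14.4% | 18.9% |

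A beta-binomial simulation (973 households of 3 nets per arm, 20,000 runs) gave 6.8% and 7.3% at ICC 0.0625, and 9.9% and 11.6% at ICC 0.2.

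**5. Effect of balance within villages on the brand contrast.** Let h be the share of variance between households within a village and v the share between villages. Village effects cancel from a contrast balanced within villages, while an unadjusted model still counts them as noise. The design effect is then about 1 + 2h − v. With h = 0.0625 and v = 0.02 (assumed) it is 1.105, giving 6.2% per pair and 6.6% for 2 df. The test is too liberal only while v < 2h. At h = 0.0625 it would hold its level at v = 0.125 and be conservative beyond that.

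**6. Single-product intervals.** Here village variation does not cancel. With 15 × 3 = 45 nets per product per village, the design effect is about 1 + 2h + 44v. Village alone at v = 0.02 (assumed) gives 1 + 44 × 0.02 = 1.88. An interval that leaves this out has 1/√1.88 = 0.73 of the proper width, about 27% too narrow. Adding h = 0.0625 gives 2.005.

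**The case against.** A reader might infer that the analysis is definitely at net level, that it ignores the randomisation, and that its p-values are too small. The documents do not go that far. The sentence names a regression and a brand factor; it does not state the unit of analysis, the variance estimator, or that brand is the only term. A logistic model with a random household intercept would also fit that description. Mixed models are named in the same section, net product is listed among the explanatory variables, and the brand sentence follows a remark about looking in more detail, so it may not be the only brand analysis. A full analysis plan, not shown, could supply the adjustment.

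Much of this stands as a limit on wording. It does not remove the point. The article does not leave the primary comparison open: it names a method, a predictor and a follow-up step, and that method as written does not match the sample size section. The mixed-model sentence serves a different purpose and specifies no random effect, so at best the text permits two different analyses of the primary question.

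Two further objections stand in full. The inflation is modest at the plan's own coefficient of variation, and the larger figures rest on correlations the protocol does not give. Balance within villages also works against the inflation, so its direction for brand contrasts is likely rather than certain.

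**Conclusion.** The brand test and the per-product intervals for attrition are specified without the household allowance that the design and sample size call for. If they are applied to nets as written, the test does not hold its nominal level. At k = 0.25 the departure is small: about 6.5% per pair and 7% for the three-brand test instead of 5%. It grows to about 10% and 12% at an assumed household correlation of 0.2. These figures assume three nets in every household, attrition near 50% and two-sided 5% testing. Balance within villages reduces them, and would reverse them if village variance exceeded twice the within-village household variance.

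The single-product intervals are the weaker part of the plan. A village correlation of only 0.02 (assumed) nearly doubles their variance, provided they are meant to describe more than the particular villages studied.

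**What to change.** Replace the brand-comparison sentence with wording such as: at each time point, brands are compared by logistic regression with household as the cluster (random intercept, GEE or cluster-robust standard errors, chosen in advance) and village as the allocation stratum; a joint 2-df test of brand is followed by pairwise contrasts from the same model.

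For the intervals, state that the 95% limits for each product's attrition and unserviceable condition use a cluster-robust variance that allows for household and village clustering. Households are nested in villages, so clustering on village covers both, and there are 7 × 10 + 6 = 76 villages. Survey variance with village as primary sampling unit is one way to do this but is not the only defensible one, because villages were chosen by proximity to district headquarters. The plan should say which population the intervals describe.

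The cost is a few lines of analysis text. Household and net identifiers are already recorded, households were drawn by village, and the named software fits these models. According to the Current study status section, only the 10-month prospective survey had been done, so the change can be fixed before the 22- and 36-month analyses and applied to all three.

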Therefore, the current study is conducted in collaboration with the Tanzanian NMCP to inform their procurement decisions. The study will be conducted in eight districts in Tanzania, selected for their demographic, geographic and ecological representativeness of the country as a whole. There will be an initial retrospective evaluation of Olyset^®^ nets distributed by the NMCP two-to-four years previously as part of both a targeted and a universal coverage campaign [25]. The same sampled households will then receive one of three LLIN products (Olyset^®^ with the new knit pattern to improve fabric strength, PermaNet^®^2.0 or Netprotect^®^) by random allocation for a prospective follow up study. Effective life of the nets will be assessed at regular intervals for three years using the WHO-recommended set of net durability variables [5] (Table 1) and a set of new methodologies (Figure 1). We will also monitor insecticide resistance in mosquito vectors as an additional component for evaluating LLIN effectiveness to contribute to the growing knowledge within Tanzania, which will assist the NMCP on rational selection of insecticides for vector control. Spatial risk factors of insecticide resistance and LLIN durability, such as land use patterns, agriculture, altitude or distance to potential breeding sites, will be assessed to determine their usefulness in selecting appropriate malaria control strategies by identifying areas where a particular LLIN intervention may be more effective than another.

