**Figure 1 Fig1:**
[figure not shown]
**Flow chart of retrospective and prospective data collection.** After study district and village selection, 45 households will be randomly selected from each village for study inclusion. After obtaining national ethical approval, community sensitisation meetings will be held and written informed consent will be obtained from each household head participating in the study. In the retrospective study in 2013, all nets from study households will be removed after an in-depth household questionnaire and 200 Olyset campaign nets will be sub-sampled for laboratory analysis of LLIN durability components (Table 1). All collected nets will be replaced with one of three new LLIN products; Olyset^®^, PermaNet^®^2.0 and Netprotect^®^ (Table 2) for the prospective study. Ten, 22 and 36 months post-distribution, every household will be followed up with a questionnaire and the presence of each study net will be affirmed to obtain attrition estimates. A random sub-sample of 48 nets per net product will be collected for subsequent analyses consisting of Ifakara Tunnel Tests, hole counts, biological efficacy tests and HPLC analysis.

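### The stated brand test names no covariate although the same households are surveyed before the new nets go out; adjustment would be a modest, free gain in precision

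*Protocol article*

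**What the plan says.** Attrition is the primary outcome: "Sample size calculations were based on the primary outcome measure of net attrition" (Sample size calculation). The Data analysis section sets the product comparison at 10, 22 and 36 months as "logistic regression with a category for each brand of net", with pairwise comparisons if the overall test is significant. No other term is named for that model.

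The randomised households are those of the retrospective study. The Background says "The same sampled households will then receive one of three LLIN products", and the legend of Figure 1 says that "all nets from study households will be removed after an in-depth household questionnaire". The Retrospective study section has the product drawn by household, giving 15 households per product in each village.

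The Data analysis section also plans generalised linear and mixed models with household survey data, and a principal component score for socioeconomic status. Their stated purpose is to find what affects durability. The list of explanatory variables mixes stable household traits (socioeconomic status, location) with variables that arise after the nets are issued (frequency of use, washing and handling, perceptions of nets).

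**The concern.** Household traits that predict net loss explain part of the variation in attrition between households. If the model contains product alone, that variation stays in the standard error of the product difference. The data that could remove some of it are collected anyway.

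The other planned models do not clearly fill the gap. They are described as a search for determinants of durability, and their pool of variables includes some that the product itself may influence. A product effect read from a model that adjusts for washing or frequency of use could lose part of the real difference between products. So the article offers a product comparison with no named covariates and a broader model with possible mediators, but no adjusted comparison restricted to traits that the product cannot change. At stake is the width of the interval for the main comparison, not its validity.

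**Working it through.** **Inputs.** From the Sample size calculation: "attrition rates of 47.5% and 52.5% with 90% power"; "Assuming an average of 3 nets per household and a coefficient of variation of 0.25"; and the result, "gives a sample size of 973 households per arm". The final size is 1,140 households per arm. Alpha is not stated; two-sided 5% is assumed. The cited page is not at hand, so the usual unmatched-cluster formula is assumed too.

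**The plan's own figure.** Households per arm = 1 + (z_α/2 + z_β)² × [p₀(1−p₀)/m + p₁(1−p₁)/m + k²(p₀² + p₁²)] / (p₀ − p₁)².

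- (1.960 + 1.282)² ≈ 10.507
- Bracket: (0.249375 + 0.249375)/3 + 0.0625 × (0.225625 + 0.275625) = 0.16625 + 0.03133 = 0.19758
- Result: 1 + 10.507 × 0.19758/0.0025 ≈ 831

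This is not 973. A coefficient of variation (CV) of about 0.36 would give 973, as would about 2.5 nets per household (971); a two-sided alpha of 2.5% gives 982. None of these is stated. Both CVs are therefore carried below. At two-sided 5% and CV 0.25, 973 households give 93.9% power.

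**How much variance lies between households.** At 50% attrition with 3 nets, s_b² = (CV × 0.5)², and the variance of a household mean is s_b² + (0.25 − s_b²)/3.

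| | CV 0.25 | CV 0.36 |
|---|---|---|
| Intracluster correlation | 0.0625 | 0.13 |
| s_b² | 0.0156 | 0.0325 |
| Variance of household mean | 0.0938 | 0.105 |
| Between-household share | 17% | 31% |

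**Gain from campaign-net retention alone.** Suppose that a household's tendency to lose nets is fully stable and that retention is also measured on 3 nets (both assumptions). The correlation between earlier and later household proportions then equals the share above.

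- CV 0.25: R² = 0.167² = 0.028. The standard error is multiplied by √(1 − 0.028) = 0.986, a fall of 1.4%. Power at 973 households goes from 93.9% to 94.5%.
- CV 0.36: R² = 0.309² ≈ 0.095. The factor is √(1 − 0.095) = 0.951, a fall of about 5%. Power goes from 90.0% to 92.6%.

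A simulation of 4,000 replicates with 973 households per arm gave variance ratios (adjusted to unadjusted) of 0.976 and 0.90. Both estimators centred on the true 5 points.

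**Gain from a whole covariate set.** If the set explains 25-50% of the between-household variance (assumption; no figure in the protocol), the variance falls by that fraction times the share.

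- CV 0.25: 0.25 × 17% to 0.50 × 17%, about 4-8%. As extra households, 1,140 × [1/(1 − gain) − 1] ≈ 50 to 104 per arm.
- CV 0.36: about 8-15%, or 96 to 209 per arm.

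**Size of chance imbalance.** The unadjusted standard error at CV 0.25 is √(2 × 0.0938/973) = 1.39 percentage points. Chance imbalance in earlier retention contributes a standard deviation of 0.167 × 1.39 = 0.23 points, already inside that standard error. At CV 0.36 the figures are 1.47 and 0.45 points.

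These calculations use household means, so they presume an analysis that allows for nets sharing a household.

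**The case against.** The strongest reply is that this is an omission in a condensed article. Naming a category for each brand does not rule out other terms, a covariate list is often left to an analysis plan that is not shown, and the same paragraph lists net product beside location and socioeconomic status in its regression models. Much of this stands: the plan does not ignore household data as a whole, and nothing is contradicted. What remains is that the article does set out a specific test for the main comparison, with product as the only named term.

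Three stronger readings are tempting, and the documents do not support them.

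- *That the unadjusted comparison is biased.* Products are drawn at random by household within village. Chance imbalance is sampling variation that a valid interval covers. Field staff pick the set on arrival and the nets may be physically distinguishable, so selective picking is conceivable, but nothing shows that it happened. Adjustment would address only the part carried by measured traits.
- *That campaign-net retention is a baseline value of the primary outcome.* The study nets are new and have no earlier attrition. Retention concerns older nets of another size and colour, and receipt is recalled by the respondent. The article does not say that the number received is recorded, and the questionnaire is not shown. It is a proxy that may not be available.
- *That power is at risk.* The protocol states "there will be at least 90% power to detect a 5% difference in attrition rates", and on its stated inputs at two-sided 5% the planned number exceeds what is needed.

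The 25-50% explained share has no support in the documents. At the stated CV, retention alone could explain at most about 17% of the between-household variance, even with a perfectly stable tendency and three nets measured.

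**Conclusion.** The point holds as a free improvement. The stated product comparison leaves out household traits that the study already collects, and so gives up a modest amount of precision. The loss from omitting earlier retention alone is about 1.4% of the standard error at CV 0.25 and about 5% at CV 0.36. For a fuller set it is about 4-8% of the variance at the stated CV, conditional on the assumed 25-50% explained share. The figures rest on attrition near 50%, three nets per household, and a two-sided 5% level where the power and the CV of 0.36 are concerned. The comparison as stated is not biased on this account, and its stated power is not threatened.

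**What to change.** State in the Data analysis section that the product model at each time point adjusts for a short fixed set of traits that the product cannot affect:

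- number of sleeping spaces, rather than nets issued, because nets are topped up after the product set has been picked;
- the principal component socioeconomic score;
- district or village, since products are allocated within village;
- retention of campaign nets, where the questionnaire yields it, with a category for households that received none.

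Exclude washing, frequency of use, perceptions of nets and any other variable that arises after allocation. Report the standardised (marginal) difference in attrition between products: an adjusted odds ratio is conditional on the covariates and does not estimate the same quantity as the unadjusted one. Keep the unadjusted result as a supporting analysis.

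The cost is analysis wording; no new data are needed. If the questionnaire does not give a usable denominator for retention, drop that covariate. At submission only the 10-month round was complete, so the set can still be fixed before the 22- and 36-month data arrive.
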